#### 6.2.2 Non-Safety Sampling

Plasma sampling for PK, and IVM testing for microvascular blood flow, will be performed at the following times:

- Predose (on the day of dosing), and
- $30 \pm 10$  minutes, and
- $2 \pm 0.25$ ,  $4 \pm 1$ ,  $8 \pm 2$ , and  $24 \pm 3$  hours, and
- $48 \pm 12$  (PK only) hours after administration of the first dose of IV GMI-1070.

Urine sampling for PK will be done over a 6-hour period starting at the beginning of the first dose.

Plasma sampling for biomarkers will be performed at the following times (samples may be frozen for later research use related to this study):

- Predose, and
- $4 \pm 1$ ,  $8 \pm 2$ ,  $24 \pm 3$ , and  $48 \pm 12$  hours after administration of the first dose of IV GMI-1070.

Outpatient follow-up visits to the clinic will take place at  $24 \pm 3$  and  $48 \pm 12$  hours post first dose, and on Day  $7 \pm 2$  and a telephone follow-up at Day  $28 \pm 3$ .

### 6.2.3 Clinical Effect

Specific details required for performance of these study evaluations and procedures may be found in the Study Operations Manual.

- IVM to measure microvascular blood flow will be performed at times specified on the study schedule.
- Biomarkers of adhesion and downstream selectin effect in the blood. Blood samples of 4 mL will be collected via direct venipuncture at times specified on the study schedule. Specific details for sample handling, storage, and shipping may be found in the Study Operations Manual.

### 6.2.4 Pharmacokinetic Samples

Blood samples of 4 mL each will be collected via direct venipuncture at times specified on the study schedule. Samples will be shipped according to the Sponsor's instructions. Specific details for sample handling, storage, and shipping may be found in the Study Operations Manual.

### 6.2.5 Review to Determine Next Dose Level

When 4 subjects have been studied (in any level) at the individual site, the data for these subjects will be reviewed by the investigator and Medical Monitor in order to determine the next dose to be administered. The data for the first 48 hours for each subject, as available, will be reviewed.

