## **3 STUDY DESIGN**

This will be an open-label, dose titration study of IV GMI-1070 in adults with stable SCD. Subjects will receive IV GMI-1070 at dose levels based on findings in earlier human studies. Study drug will be administered in the Clinical Research Center (CRC), day hospital, or equivalent clinical setting.

Titration for this study may be done either up or down and not necessarily in a step-wise fashion. At the beginning of the study, 4 subjects at each site will receive Dose Level A, which consists of a 20 mg/kg loading dose of IV GMI-1070 followed by a single 10 mg/kg dose of IV GMI-1070. Thus, subjects will

receive a total of 2 doses: 1 loading dose (20 mg/kg) in the morning at 0 hours, and 1 single dose (10 mg/kg) in the evening at  $10 \pm 1$  hours.

After these first 4 subjects at each site have been treated, safety, PK, and blood flow data from this first group will be reviewed by the investigator and the Medical Monitor. After this review, a site-specific decision will be made to do one of the following:

- Enroll 4 more subjects at this dose level (continue at Dose Level A); OR
- Enroll 4 subjects at the higher dose level (Dose Level B, 40 mg/kg loading dose followed by 20 mg/kg for 1 dose); OR
- Enroll 4 subjects at any of the 2 lower dose levels (Dose Level C, 10 mg/kg loading dose followed by 5 mg/kg for 1 dose; or Dose Level D, 5 mg/kg loading dose followed by 2.5 mg/kg for 1 dose).

Safety, PK, and blood flow data will be reviewed after completion of each group of 4 subjects at each site. At that time a decision will be made to do one of the following:

- Enroll 4 more subjects at the current dose level; OR
- Evaluate titration options and enroll 4 subjects at any other protocol-described dose level.

This process will continue until a total of 20 subjects have been treated with GMI-1070. Refer to Figure 3 in Section 3, Study Titration Flow, for a diagram of study drug dosing at each site.

Note: If enrollment at a site begins after other sites have enrolled in the study, the safety, PK, and blood flow information gained by early-enrolling site(s) may be used to modify dosing by later-enrolling site(s).

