**Table 3: Data Reviewed to Determine Next Dose Level**

|                        | Safety                                         | PK                                            | Effect                                        |
|------------------------|-------------------------------------------------------|------------------------------------------------------|------------------------------------------------------|
| Data to review: | Physical examination, AEs, clinical labs, vital signs | GMI-1070 plasma levels                               | IVM data                                             |
| To determine:   | If dose-limiting toxicity is seen*                    | If plasma levels are consistent with expected levels | If difference in IVM data is seen pre- and post-dose |

\*Dose-limiting toxicity is defined in Section 7.4.

Based on review of these data, and determination of the above, dosing may continue as follows using 1 of the dose levels described in this protocol:

- If dose-limiting toxicity is seen, the decision will be made based on safety data.
  - If dose-limiting toxicity is seen, and continued dosing at a lower dose level is believed to be appropriate (as determined by the investigator and Medical Monitor), the study may continue at a lower dose level.
  - If dose-limiting toxicity is seen, and continued dosing at any level is not warranted (as determined by the investigator and Medical Monitor), the study will be halted for further review of the data.
- If no dose-limiting toxicity is seen, the decision will be made based on effect data.
  - If a microvascular blood flow effect is not clearly detectable by IVM, the study may continue at the same dose to gather more data, or increase to a higher dose level.
  - If a microvascular blood flow effect is clearly detectable, the study may continue at the same dose, or decrease to a lower dose level.

Any individual site safety concerns discussed, that could have a more global impact, will be shared among all participating sites.

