#### **9.2.8 Investigational Product Interim Analysis**

An interim analysis will be performed by site. An interim analysis will be done after every fourth subject at each clinical site completes the study to determine whether to change the dose level for the next group of 4 at that site. These 4 subjects will be examined to determine whether the dose of GMI-1070 was safe and effective (see Section 6.2.5). PK data will also be analyzed at this time. This analysis will be repeated for each group of 4 subjects at the clinical site level.

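### The next-dose review judges dose-limiting toxicity on one site's own 4 subjects, so after one or two related Grade 3 events at a dose level nothing binding stops a DLT-free site from escalating

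*Protocol*

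**What the plan says.** The unit of review is the site. Section 3 states that after the first 4 subjects at each site "a site-specific decision will be made to do one of the following": stay at Level A, go up to B, or go down to C or D. Section 6.2.5 has the data for the 4 subjects studied "at the individual site, the data for these subjects will be reviewed by the investigator and Medical Monitor". Section 9.2.8 performs the interim analysis by site: "These 4 subjects will be examined to determine whether the dose of GMI-1070 was safe and effective", and the purpose is "to determine whether to change the dose level for the next group of 4 at that site".

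The list under Table 3 in Section 6.2.5 turns the review into a decision. After a DLT, either "the study may continue at a lower dose level" or dosing is halted for further review. Otherwise, "If no dose-limiting toxicity is seen, the decision will be made based on effect data", and where no blood-flow effect is clearly detectable by intravital microscopy (IVM), "the study may continue at the same dose to gather more data, or increase to a higher dose level".

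Section 7.4 defines a DLT as a treatment-emergent event of Grade 3 to 5 that is probably or definitely related, without reference to site. For related toxicities the study is halted temporarily on 2 Grade 3 events in one subject, 3 Grade 3 events within a dose level, any Grade 4 or 5 event, or a vaso-occlusive crisis within 24 hours of dosing in 2 subjects.

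Three provisions link the sites. The Synopsis requires consensus between investigator and Medical Monitor before proceeding. Site safety concerns are shared with all sites; Section 6.2.5 limits this to concerns with possible wider impact. Section 3 allows, but does not require, later-enrolling sites to use earlier sites' data.

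**The concern.** A DLT is information about the dose, and every site using that dose needs it. Safety is the primary objective (Section 2.2.1), and Section 2.1 calls this a first evaluation in sickle cell patients. If whether a DLT has been seen is answered from one site's 4 subjects, two sites at the same level can reach opposite answers. One is confined to lower doses or a halt, while the other enters the branch in which a higher dose is allowed. The protocol leaves open whether a DLT at the first site should count at the second, at the point where the dose may double.

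**Working it through.** **Step 1. The units side by side.**

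| Protocol text | Unit |
|---|---|
| Section 3, decision after each group | Site |
| Section 6.2.5, data reviewed | 4 subjects at one site |
| Section 9.2.8, interim analysis | 4 subjects at one site |
| Section 6.2.5, consequences of a DLT | The study |
| Section 7.4, DLT definition | No site mentioned |
| Section 7.4, halt on 3 Grade 3 events | Dose level |
| Section 7.4, other halts | One subject, any one event, or 2 subjects |

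No sentence says whether a DLT at one site counts as seen in another site's review.

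**Step 2. What the halts leave open.** One related Grade 3 event, or two in different subjects at the same level, are DLTs but meet none of the four halt rules. They can change dosing only through the Section 6.2.5 review.

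**Step 3. Example.** At Level A, site 1 has 1 of 4 subjects with a related Grade 3 event and site 2 has 0 of 4. The level total is 1, below 3, so there is no halt. Site 1 may go lower or halt. Site 2, judged on its own group and without a clear IVM effect, may go to Level B.
- Total dose at A: 20 + 10 = 30 mg/kg. At B: 40 + 20 = 60 mg/kg. Ratio 60/30 = 2.
- Site 1's next group would receive C (10 + 5 = 15 mg/kg) or D (5 + 2.5 = 7.5 mg/kg). Against B the ratios are 60/15 = 4 and 60/7.5 = 8.

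**Step 4. What a look at 4 can see.** The protocol gives no DLT rate or operating characteristic, so there is no stated figure to reproduce. Assume a true DLT rate p, independent subjects, and all three sites (Synopsis) treating 4 each at Level A, 12 in total. The chance of no DLT in n subjects is (1 − p)^n.

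| Assumed p | One site, n = 4 | Pooled, n = 12 |
|---|---|---|
| 5% | 0.95^4 = 0.815 | 0.95^12 = 0.540 |
| 10% | 0.90^4 = 0.656 | 0.90^12 = 0.282 |
| 20% | 0.80^4 = 0.410 | 0.80^12 = 0.069 |

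For scale, Section 1.6.1 reports no event above Grade 2 among 54 active healthy subjects. The one-sided 95% upper limit for 0/54 is 1 − 0.05^(1/54) = 5.4%. The rate in sickle cell patients is unknown.

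**Step 5. How often the configuration could arise.** Add the assumption of one Grade 3 event per affected subject. With 1 or 2 affected among three sites, at least one site is always clean, so the chance is 12p(1 − p)^11 + 66p²(1 − p)^10: 44%, 61% and 49% at p = 5%, 10% and 20%. For one named site to be clean with 1 or 2 affected among the other 8, it is (1 − p)^4 × [8p(1 − p)^7 + 28p²(1 − p)^6]: 27%, 35% and 26%. These are chances that the gap is open, not that anyone escalates.

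**The case against.** The strongest reply is that the consequences in Section 6.2.5 are worded for the study. Read literally, a DLT at any site moves or halts the whole study, and another site's escalation would conflict with that. This stands in part: the fault is a conflict of scope, and a reader who infers that the protocol positively authorises escalation past a known DLT goes too far. But the same section feeds the decision with one site's data, and Sections 3 and 9.2.8 call it that site's decision, so the literal reading does not settle the matter.

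Second, the reviews are not sealed off from each other. The Medical Monitor joins every one, consensus is needed to proceed, and safety concerns are shared. The investigator (for safety) or the Sponsor (for any reason) may deem continuing inappropriate. Section 6.2.5 also does not exclude other sites' data. A careful Medical Monitor would probably hold the dose. All of this stands as mitigation, but it permits the hold without requiring it.

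Third, a reader might infer that the 8 of 12 subjects at other sites are ignored for safety. They are not: their Grade 3 events count towards the dose-level halt, any related Grade 4 or 5 event halts the study wherever it occurs, and concerns are shared. Nor does Section 7.4 count all toxicity by dose level; only one of its four halt rules does.

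Fourth, Level B lies within a regimen already given to healthy subjects (a 40 mg/kg load, then 20 mg/kg doses for 2 days; Section 1.6.1). That tempers the concern, although the population is new.

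Finally, 12 subjects at Level A is one scenario among several for five groups of 4. Section 3 lets a new site start at a level already chosen elsewhere, and rates of 10% and 20% exceed the healthy-volunteer limit of 5.4%.

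**Conclusion.** The point holds for one situation: one or two related Grade 3 events, in different subjects, at the same dose level. There the site-level review, the study-level wording of the consequences and the dose-level halt rule do not fit together, and no binding rule stops a DLT-free site without a clear IVM effect from going to a higher dose. From Level A that is a doubling.

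The size can only be illustrated. At assumed rates of 10% and 20%, a site's own 4 subjects show no DLT 66% and 41% of the time, against 28% and 7% for the pooled 12, provided all three sites treat 4 at Level A. The 44% to 61% in Step 5 should not be read as a probability of escalation: actual escalation also needs no clear IVM effect and the agreement of the investigator and Medical Monitor. Because those safeguards are real, this is a gap worth closing rather than a fatal flaw in the design.

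**What to change.** Amend Section 6.2.5, with matching text in Sections 3 and 9.2.8:

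- Whether a DLT has been seen is judged on all subjects treated so far at that dose level or lower, at all sites.
- No site may escalate above a level at which a DLT has been seen at any site unless the Medical Monitor has reviewed the pooled data with that site's investigator and their agreement is documented.

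Site-specific choice can stay for the effect branch. Agreement by the investigators of all active sites is not needed.

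The cost is a short amendment, with no extra subjects, visits or samples. A site may wait briefly for other sites' safety data before escalating. The pooled criterion will also prompt the extra review more often when the true rate is low (at 5%, no DLT in 54% of pooled looks at 12 against 81% of looks at 4), but documented agreement still leaves escalation open.

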**Table 3: Data Reviewed to Determine Next Dose Level**

|                        | Safety                                         | PK                                            | Effect                                        |
|------------------------|-------------------------------------------------------|------------------------------------------------------|------------------------------------------------------|
| Data to review: | Physical examination, AEs, clinical labs, vital signs | GMI-1070 plasma levels                               | IVM data                                             |
| To determine:   | If dose-limiting toxicity is seen*                    | If plasma levels are consistent with expected levels | If difference in IVM data is seen pre- and post-dose |

\*Dose-limiting toxicity is defined in Section 7.4.

Based on review of these data, and determination of the above, dosing may continue as follows using 1 of the dose levels described in this protocol:

- If dose-limiting toxicity is seen, the decision will be made based on safety data.
  - If dose-limiting toxicity is seen, and continued dosing at a lower dose level is believed to be appropriate (as determined by the investigator and Medical Monitor), the study may continue at a lower dose level.
  - If dose-limiting toxicity is seen, and continued dosing at any level is not warranted (as determined by the investigator and Medical Monitor), the study will be halted for further review of the data.
- If no dose-limiting toxicity is seen, the decision will be made based on effect data.
  - If a microvascular blood flow effect is not clearly detectable by IVM, the study may continue at the same dose to gather more data, or increase to a higher dose level.
  - If a microvascular blood flow effect is clearly detectable, the study may continue at the same dose, or decrease to a lower dose level.

Any individual site safety concerns discussed, that could have a more global impact, will be shared among all participating sites.

## **7 ADVERSE AND SERIOUS ADVERSE EVENTS**

### **7.1 Safety Monitoring**

All AEs occurring from enrollment through Day 28  $\pm$  3 will be recorded. An AE is any unintended medical occurrence in a subject or clinical investigation subject administered a pharmaceutical product that does not necessarily have a causal relationship with this treatment (International Conference on Harmonisation/World Health Organization [ICH/WHO]). An AE can, therefore, be any unfavorable and unintended sign (including an abnormal laboratory finding, for example), symptom, or disease temporally associated with the use of a medical product, whether or not considered related to the medical product (ICH/WHO).

The subjects will be instructed to inform the investigator or clinic staff of any AEs and intercurrent illnesses experienced during the trial. The inquiry will be posed in a non-specific manner using open-ended questions so as not to bias the response (eg, How are you today?).

Patients with SCD, as a result of this condition, commonly have abnormal values for hemoglobin, hematocrit, WBC count, bilirubin, aspartate transaminase (AST,

also known as SGOT), LDH, CRP, hematuria, and other laboratory and clinical findings. It is assumed that abnormalities in physical exam or laboratory findings consistent with the subject's underlying diagnosis of SCD will be present prior to dosing and therefore will not be treatment-emergent AEs (TEAEs). However, if changes believed to be related to the diagnosis of SCD occur after the initiation of dosing, the investigator shall note whether they are considered AEs (clinically significant changes) or not clinically significant, and if designated as AEs, the relationship to GMI-1070.

Any subject who has an AE (whether serious or non-serious) will be evaluated by the investigator, or other monitoring physician, and will be treated, referred to the subject's own physician, and/or followed up until the symptoms or values return to normal or acceptable levels, as judged by the investigator. A physician, either at the study clinic or at a nearby hospital emergency room, will administer treatment for any SAEs. Where appropriate, medical tests and examinations will be performed to document resolution of event(s).

Pregnancy occurring during a study in a female study subject will be documented in a note to file and reported as a protocol deviation to the Institutional Review Board (IRB). Pregnancy itself is not an SAE but will be reported as an AE. The investigator or designee will discontinue the pregnant subject from the treatment aspects of the study (PK testing, IVM, and IV GMI-1070 administration), continue to follow her per protocol for safety outcomes only, and advise her to seek prenatal care and counseling from her primary care provider.

The site clinical staff will request the pregnant subject to notify the site of the outcome of the pregnancy (ie, birth, loss, or termination). To help ensure this, the site clinical staff will follow-up with the subject until the end of pregnancy, with the subject's consent. This request and the subject's response will be documented in the subject's source document.

## **7.2 Reporting**

All AEs occurring during this clinical trial will be recorded. The investigator will review each event and assess its relationship to drug treatment (unrelated, remote, possible, probable, or definite). Worsening of pre-treatment events after initiation of investigational product must be recorded as new AEs.

Each sign or symptom reported will be graded in accordance with the WHO Common Toxicity Criteria (Appendix 1) where Grade 1 = mild, Grade 2 = moderate, Grade 3 = severe, Grade 4 = life-threatening or disabling, and Grade 5 = death related to AE. The date of AE onset, time of onset, duration, severity, relationship, outcome, and use of concomitant treatment will be recorded for each event.

For the purposes of this study, VOC shall be defined as an episode requiring a visit to a medical facility resulting in medical treatment for pain. It is recognized that VOC and pain are frequent and expected events in SCD, and the use of narcotics for these episodes is often required and considered routine. When determining grade of an AE for VOC or pain, the investigator shall use the following classification (noted below), rather than the need for narcotics as described in the WHO Common Toxicity Criteria.

If the AE does not have a toxicity grade listed in Appendix 1, the following severity classifications will be used.

- Mild - The AE is easily tolerated and does not interfere with daily activity
- Moderate - The AE interferes with daily activity, but the subject is still able to function
- Severe - The AE is incapacitating and requires medical intervention

The relationship of each AE to study drug will be assessed using the following definitions:

Definite:

- Distinct temporal relationship with drug treatment
- Event cannot be explained by subject's clinical state or other factors

Probable:

- Reasonable temporal relationship with drug treatment
- Event cannot easily be explained by subject's clinical state or other factors

Possible:

- Reasonable temporal relationship with drug treatment
- Event could be explained by subject's clinical state or other factors

Remote:

- Poor temporal relationship with drug treatment
- Event easily explained by subject's clinical state or other factors

Unrelated:

- Event occurring before dosing
- Event or intercurrent illness due wholly to factors other than drug treatment

